10.8.2. Early Termination of Part or All of the Study

The study may be terminated prematurely in the event of unexpected serious adverse events (with or without necessitating a review of the product’s safety profile), or if unforeseen events or new information about the product suggest that the study objectives are unlikely to be achieved. Such circumstances may lead the sponsor to halt the study early. CHU Amiens-Picardie (the sponsor) reserves the right to stop the study at any time if it becomes apparent that enrollment objectives are not being met. In case of premature discontinuation of the study, the sponsor will inform the ANSM and the Ethics Committee (CPP) within 15 days.

10.9. Study-Related Constraints and Participant Compensation

A person participating in this research may take part in another study concurrently, except they may not participate in another interventional therapeutic trial, for a period of 2 days after the surgery. No compensation is planned for participants in this study.

11. MANAGEMENT OF ADVERSE EVENTS AND NEW FINDINGS

11.1. Definitions

Adverse Event (AE) (per Article R1123-46 of the Public Health Code): Any harmful event occurring in a person participating in a research study involving human subjects, whether or not the event is related to the research or the product under study

.

Adverse Effect (per Article R1123-46): An adverse event occurring in a person participating in a research study, when that event is related to the research or the product under study.

Serious Adverse Event (SAE): Any adverse event that:

• results in death,

• is life-threatening,

• requires hospitalization or prolongation of existing hospitalization,

• causes a significant or persistent disability or incapacity,

• causes a congenital anomaly or birth defect,

• or any event considered medically serious (for a drug, regardless of dose administered). (“Life-threatening” refers to an immediate risk of death at the time of the event.)

Unexpected Adverse Effect:

For drug studies: any adverse effect of the drug that is not consistent in nature, severity, frequency, or outcome with the reference safety information (as in the Summary of Product Characteristics or the Investigator’s Brochure for an unauthorized product).

For studies on a medical device or in vitro diagnostic device: any adverse effect of the device not consistent in nature, severity, or outcome with the information in the device’s instructions for use or Investigator’s Brochure.

For other human research (not involving drugs or devices): any adverse effect whose nature, severity, or outcome is not consistent with the information relating to the products, procedures, or methods used in the research.

New Finding (Fait nouveau) (Article R1123-46): Any new information that could lead to a reassessment of the benefit/risk ratio of the research or the product under study, or that could warrant changes in the use of the product, in how the research is conducted, or in the documents related to the research, or could justify suspending, interrupting, or modifying the research protocol.

11.2. Description of Expected Serious Adverse Events

The expected serious adverse events in this context are those related to the practice of regional anesthesia and the use of IV lidocaine and epidural ropivacaine. These include systemic toxicity from local anesthetics, severe allergic reactions to local anesthetics, and infections at the epidural puncture site.

11.3. Procedures in Case of Adverse Event or New Finding

The investigator will assess each adverse event for its severity. The investigator must notify the sponsor without delay upon becoming aware of any serious adverse event or any new finding, if it occurs:

from the date of consent signature, during the entire planned follow-up duration for the patient in the study, indefinitely, if the event might be attributable to the investigational treatment.

Notification should follow these guidelines:

| Type of Event | Notification Method | Timeline for Notification to Sponsor |
| --- | --- | --- |
| Non-serious AE | Document in the CRF | No immediate notification (report in CRF only) |
| SAE (expected) | Initial SAE report form (+ written report if needed) | Immediate notification to sponsor |
| SAE (unexpected) | Initial SAE report form (+ written report if needed) | Immediate notification to sponsor |
| New Finding | New finding report form (+ written report if needed) | Immediate notification to sponsor |
| Pregnancy (during or shortly after study) | Pregnancy notification form | Upon confirmation of pregnancy |

Sponsor / Vigilance Unit Contact:

Clinical Research and Innovation Directorate, CHU Amiens-Picardie

[contact] – [contact]

Email: [contact] All such events will be followed until complete resolution. Additional information (via follow-up report form) regarding the outcome of the event, if not known at the time of the initial report, will be sent to the sponsor by the investigator. Note: Occurrence of a pregnancy during or immediately after the study is not in itself classified as an SAE. However, any pregnancy must be reported in the same manner as an SAE because it requires special follow-up. Any abnormality observed in the fetus or child will be reported. Any voluntary termination of pregnancy (elective abortion), medically indicated termination, or miscarriage must be reported via a pregnancy form, and if it required hospitalization, it should also be reported as an SAE following the same timelines.

11.4. Reporting and Recording of Unexpected SAEs and New Findings

The sponsor (or designated vigilance unit) will report all unexpected SAEs and new findings that occur during the study to the ANSM and the competent Ethics Committee (CPP) within the following timeframes:

For an unexpected serious adverse effect that results in death or is life-threatening: without delay upon the sponsor becoming aware of it.

For other unexpected serious adverse effects: no later than 15 days from when the sponsor became aware of them. The sponsor will submit relevant follow-up information in the form of a safety report to ANSM. In the case of a suspected unexpected serious adverse reaction (SUSAR) that resulted in death or was life-threatening, follow-up information will be reported within 8 days of the initial report; for other SUSARs or a new finding, follow-up information will be reported within 8 days after the 15-day deadline mentioned above. The Ethics Committee (CPP) will ensure, if necessary, that participants are informed of adverse events and that they reconfirm their consent to continue in the study. For drug studies, the sponsor/vigilance unit will also record all unexpected SAEs in the EudraVigilance database. In the case of a blinded study (not applicable here), the sponsor would break the blind for reporting SAEs to ANSM and CPP

11.5. Annual Safety Report

On the anniversary date of the study’s regulatory authorization, the sponsor will prepare an annual safety report that includes:

A list of all serious adverse events that are deemed to be related to the investigational drug(s) (including both expected and unexpected serious events).

A concise, critical analysis of the safety of participants enrolled in the research.

This report will be sent to ANSM and the CPP within 60 days after the anniversary date of the study’s authorization

12. STATISTICAL ASPECTS

12.1. Calculation of Study Size

We anticipate that the proportion of patients with ropivacaine or lidocaine concentrations outside the safe range will be low. Assuming this proportion is around 10%, enrolling 50 patients would allow us to estimate this percentage with a confidence interval whose width does not exceed 16% (i.e., ±8% precision).

In any scenario, the percentage can be estimated with a precision no worse than ±14% (the worst-case precision corresponds to a proportion near 50%).

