7.2. Exclusion Criteria

Exclusion criteria are:

Abdominal surgery via laparoscopy.

Contraindication to high lumbar/thoracic epidural placement (e.g., coagulation disorder, localized or systemic sepsis, shock or uncorrected hypovolemia, respiratory failure if block level above T7, severe aortic or mitral stenosis, obstructive cardiomyopathy, severe uncompensated heart failure, infection at puncture site).

Contraindication to IV lidocaine: allergy to local anesthetics, acute porphyria, unpaced atrioventricular conduction disorders, severe heart failure, severe liver failure, uncontrolled epilepsy, concomitant therapy with class I antiarrhythmic.

Contraindication to ropivacaine: allergy to local anesthetics, acute porphyria.

Failure to successfully place the epidural.

Major hepatectomy with vascular clamping.

Patient under 18 years of age.

Patient under legal protection (guardianship) or deprived of liberty.

Patient who is pregnant or breastfeeding.

Patient refusal to participate.

Patient not affiliated with a social security system.

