12.2. Statistical Methods

Quantitative variables will be described as mean ± standard deviation and median [range]. Qualitative variables will be described as percentages with 95% confidence intervals

Primary endpoint analysis: We will calculate the percentage of patients who have at least one plasma concentration of ropivacaine or lidocaine outside the safe range. A 95% confidence interval (using an asymptotic or exact method as appropriate) will be computed for this percentage.

Secondary endpoint analysis: The percentage of patients experiencing a toxic event will be calculated with a 95% confidence interval (asymptotic or exact method). All statistical analysis will be performed using SAS software version 9.4

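### With 50 patients and about 10% of them out of range, no standard 95% confidence interval is as narrow as the 16 points stated; the ±14-point worst case holds for asymptotic intervals but not for the exact one

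*Protocol*

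**What the plan says.** Protocol section 12.1 (Calculation of Study Size) takes a proportion of about 10% and gives the whole case for the sample size in one statement: "enrolling 50 patients would allow us to estimate this percentage with a confidence interval whose width does not exceed 16% (i.e., ±8% precision". It then adds a bound meant to hold whatever the result: "In any scenario, the percentage can be estimated with a precision no worse than ±14" percentage points, with the worst case placed near 50%. The statistical paragraph of the summary (section 1) makes the same two claims. There is no hypothesis test and no other basis for 50.

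Section 12.2 (Statistical Methods) defines the quantity to be estimated: "We will calculate the percentage of patients who have at least one plasma concentration of ropivacaine or lidocaine outside the safe range". On the interval it says: "A 95% confidence interval (using an asymptotic or exact method as appropriate) will be computed for this percentage". The secondary endpoint is given the same choice of methods. The text does not say when each applies.

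**The concern.** The 16-point figure is worded as a ceiling, not as an approximation, so it can be checked directly, and the usual formula gives more than 16. The count expected at 10% is 50 × 0.10 = 5 patients. At so small a count the common interval methods differ noticeably, and section 12.2 leaves both families of method available. The stated precision should therefore match an interval that the analysis may actually report.

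What is at stake is the accuracy of the only justification for the sample size. The study sets out to show that the combination is safe, so readers will look at the upper end of the interval. A symmetric ±8 around 10% suggests a range ending near 18%. The exact interval for the same data ends at 21.8%.

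**Working it through.** **Inputs.** n = 50 and p = 0.10 (section 12.1); two-sided 95% level, so z = 1.96 (section 12.2); one binary outcome per patient (section 12.2).

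**Step 1: the plan's own figure.** The Wald half-width is z × √(p(1−p)/n).

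- At p = 0.10: 1.96 × √(0.10 × 0.90 / 50) = 0.0832, that is ±8.3 points, width 16.6.
- The stated ±8 and 16 appear only if 8.3 is rounded down to 8 and then doubled. A 90% level does not explain them either (±6.98).
- Patients needed for a Wald width of 16 or less: 1.96² × 0.09 / 0.08² = 54.02, so 55.

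**Step 2: other standard 95% intervals at 5/50.**

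| Method | Interval | Width (points) | Distance below / above 10% |
|---|---|---|---|
| Wald | 1.7% to 18.3% | 16.6 | 8.3 / 8.3 |
| Jeffreys | 3.9% to 20.5% | 16.6 | 6.1 / 10.5 |
| Wilson | 4.3% to 21.4% | 17.0 | 5.7 / 11.4 |
| Agresti-Coull | 3.9% to 21.8% | 17.9 | 6.1 / 11.8 |
| Clopper-Pearson (exact) | 3.3% to 21.8% | 18.5 | 6.7 / 11.8 |

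Every width is above 16. To bring it to 16 or less at 10%, Wilson needs 57 patients, and Clopper-Pearson needs 66 (treating 0.1n as continuous).

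**Step 3: the worst case, 25/50.**

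- Wald: 1.96 × √(0.25 / 50) = 0.1386, so ±13.9. The stated ±14 is reproduced.
- Wilson: ±13.4.
- Clopper-Pearson: 35.5% to 64.5%, so ±14.5. The stated ±14 is exceeded; 54 patients would be needed.

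**Step 4: sensitivity of ±14 to lost patients.** Wald gives 13.9997 at n = 49 and 14.14 at n = 48. Wilson stays within 14 down to n = 46 (13.88) and passes it at n = 45 (14.02).

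**Step 5: does the method matter at low counts?** At 0/50, Wald collapses to 0% to 0%, while the exact upper limit is 7.1%. At 1/50 the upper limits are 5.9% (Wald) and 10.6% (exact). Summing binomial probabilities at n = 50, the true coverage of the nominal 95% Wald interval is 88% when p = 10% and 64% when p = 2%. For Clopper-Pearson it is 97% and 98%.

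**The case against.** The strongest defence is that the slip is tiny. The authors evidently used the usual planning formula, and 8.3 rounds to 8. Section 12.1 speaks of a proportion around 10%, and at 4/50 (8%) the Wald width is 15.0 and the Wilson width 15.7, both within 16. The figure of 18.5 comes from holding an exact interval against a claim that was evidently built on Wald. Most of this stands and sets the severity. It does not rescue the sentence, which states a ceiling at 10% that even its own formula exceeds.

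A second defence is that "using an asymptotic or exact method as appropriate" would ordinarily be read as exact for small counts, and that naming the interval is commonly left to an analysis plan, which is not at hand. That is fair, so the open choice is not a fault in its own right here. It matters because the precision claim does not fit either option. If exact is the natural reading at 5 expected events, the stated precision is further off, not closer.

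Three stronger readings are tempting, and the document supports none of them.

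- A reader might infer that the 16.6-point interval is lopsided. It is the Wald interval and is symmetric; the asymmetry belongs to the exact and score-type intervals.
- A reader might infer that losing any patient breaks the ±14 bound, since "Failure to successfully place the epidural" is an exclusion that becomes known only in the operating room, after consent, and section 10.8.1 lets data be excluded for major deviations. But Wald still meets ±14 with 49 patients. The Protocol gives no loss rate and does not say whether such patients count towards the 50.
- A reader might infer that the method would be picked to flatter the result. Nothing in the Protocol suggests this. The study is descriptive and sections 12.1 and 12.2 set no success threshold.

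**Conclusion.** The precision claim at 10% is wrong as written: none of the standard 95% intervals checked is 16 points wide or less at 5/50. The excess is 0.6 points of width by Wald and 2.5 points by Clopper-Pearson. The worst-case claim is correct for asymptotic intervals with 50 patients and wrong by about 0.5 points for the exact interval. These results assume that all 50 patients are evaluable and, for the 16-point figure, that exactly 10% is observed.

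Severity is minor. The sample size, endpoint and design are unaffected, and under the planning formula the cause is a rounding slip. It is still worth correcting, because these sentences are the only support offered for 50 patients.

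**What to change.** Keep 50 patients. In section 12.1 and in the summary, replace both precision statements with wording such as: for 50 evaluable patients, at 10% observed the exact 95% CI is 3.3% to 21.8% (width 18.5 points); the worst case is about ±14.5 points; with no events the upper limit is 7.1%.

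In section 12.2, name one non-Wald interval, Clopper-Pearson or Wilson, for both the primary and secondary endpoints, so that the analysis matches the restated figures. If Wilson is chosen, the figures to quote are 4.3% to 21.4% (width 17.0) at 10%, ±13.4 at worst, and an upper limit of 7.1% with no events.

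This is a change of wording only. The one downside is a slightly less favourable stated precision.

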12.2. Statistical Methods

Quantitative variables will be described as mean ± standard deviation and median [range]. Qualitative variables will be described as percentages with 95% confidence intervals

Primary endpoint analysis: We will calculate the percentage of patients who have at least one plasma concentration of ropivacaine or lidocaine outside the safe range. A 95% confidence interval (using an asymptotic or exact method as appropriate) will be computed for this percentage.

Secondary endpoint analysis: The percentage of patients experiencing a toxic event will be calculated with a 95% confidence interval (asymptotic or exact method). All statistical analysis will be performed using SAS software version 9.4

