OBJECTIVES: The primary objective of this study is to evaluate the plasma concentrations of lidocaine and ropivacaine during the combination of an epidural anesthesia and intravenous lidocaine in a major abdominal surgery. The secondary objective is to investigate the undesirable side effects related to local anesthetics when combining epidural anesthesia with intravenous lidocaine during a major abdominal surgery (central nervous system effects: seizures, dizziness, convulsions, paresthesia, tongue numbness, hyperacusis, tinnitus, visual disturbances, dysarthria, muscle contractions, tremors; hypoesthesia; cardiac disorders: bradycardia, tachycardia, conduction disturbances possibly progressing to cardiac arrest). STUDY DESIGN: Before general anesthesia, patients undergoing major abdominal surgery via laparotomy will have a thoracic epidural catheter placed; however, no injection through the catheter will occur during the surgery. During surgery, patients will receive an intravenous bolus of lidocaine at 1.5 mg/kg (SFAR recommendations), followed by a continuous IV infusion of lidocaine at 2 mg/kg/h (SFAR recommendations), which will be stopped 30 minutes before the end of surgery (at the time of surgical closure). The epidural ropivacaine infusion will be started at the same time the lidocaine infusion is stopped, using ropivacaine 1 mg/mL with an initial minimum bolus of 5 mL, then maintained at a minimum rate of 5 mg/h via the epidural catheter for up to 24 hours postoperatively. The rest of the anesthetic protocol is at the discretion of the anesthesiologist in charge of the patient. As part of the study, blood samples will be taken to measure lidocaine plasma levels: 30 minutes after the induction bolus, at the time the continuous lidocaine infusion is stopped, and 2 hours after the start of the epidural ropivacaine infusion. Blood samples to measure ropivacaine plasma levels will also be taken 2 hours after the start of the epidural and 24 hours after the start of the epidural.

INCLUSION CRITERIA:

Patient undergoing major abdominal surgery with laparotomy

Age ≥ 18 years

Written informed consent obtained

Affiliated to a social security system (health insurance)

EXCLUSION CRITERIA:

Major abdominal surgery via laparoscopic approach

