3.3. Rationale for Methodological Choices

Lidocaine and ropivacaine are both metabolized in the liver. The toxic thresholds for these two local anesthetics are becoming well known: for lidocaine, the therapeutic plasma range is 1.4 to 5 µg/mL, and toxicity can begin at concentrations above 5 µg/mL. Neurotoxic effects appear around 15 µg/mL and cardiotoxicity around 21 µg/mL. For ropivacaine, the usual maximal total venous concentration not to exceed is about 2.2 µg/mL. The half-life of IV lidocaine is 80–110 minutes. Ropivacaine, when administered into the epidural space, is absorbed completely in a biphasic manner, with half-lives of approximately 14 minutes and 4 hours for the two phases in adults. Its slow absorption is the rate-limiting step in its elimination, leading to a longer apparent elimination half-life after epidural administration compared to IV administration. In our study, five plasma measurements of lidocaine and ropivacaine will be taken at different times during surgery and up to 24 hours post-op: lidocaine level at 30 minutes after the bolus, lidocaine level at the end of its infusion (i.e. at surgical closure), lidocaine level at 2 hours after starting the epidural, ropivacaine level at 2 hours after starting the epidural, and ropivacaine level at 24 hours after starting the epidural. Achieving a steady plasma level during a continuous infusion takes more than 60 minutes, which is why an initial bolus is recommended. Given the rapid distribution after a bolus, it’s recommended to start the maintenance continuous infusion promptly if a stable plasma concentration is to be maintained for infusions longer than 20 minutes. This justifies our first blood draw at 30 minutes after the lidocaine bolus. Thereafter, the plasma concentration remains stable around a level determined by the dose and infusion rate, which is why we will measure at the moment of stopping the infusion to capture the intraoperative plasma level of lidocaine. For the epidural, systemic absorption is gradual. Studies show a linear increase in plasma levels during the continuous infusion; the 2-hour ropivacaine level will provide an initial indication of ropivacaineemia. The lidocaine sample taken at the same 2-hour mark will indicate the residual lidocaine concentration at the time ropivacaine levels are rising, giving insight into the overlap period of both local anesthetics, and whether lidocaine’s decline follows the expected pattern when another local anesthetic is present. Finally, the ropivacaine level at 24 hours post-epidural induction will reflect the average plasma concentration after a full day of continuous epidural ropivacaine infusion. Lidocaine is not measured at 24h because it will have been fully eliminated by that time.

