5. ENDPOINTS

5.1. Primary Endpoint

The primary endpoint is the plasma concentration of ropivacaine and lidocaine falling outside the safe range at the various time points of patient management. We will obtain five plasma measurements of lidocaine and ropivacaine at different times during surgery and up to 24 hours postoperatively: lidocaine level at 30 minutes after the bolus injection, lidocaine level at the end of its infusion (i.e. at surgical closure), lidocaine level at 2 hours after induction of the epidural, ropivacaine level at 2 hours after induction of the epidural, and ropivacaine level at 24 hours after induction of the epidural. The toxic thresholds of these two local anesthetics are known: for lidocaine, the safe plasma range is 1.4 to 6 µg/mL; neurotoxicity appears from 15 µg/mL and cardiotoxicity from 21 µg/mL. For ropivacaine, the usual maximum total venous concentration not to exceed is around 2.2 µg/mL. Any single measurement above the toxicity threshold will be considered an occurrence of toxicity.

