8. STUDY TREATMENTS/STRATEGIES/PROCEDURES

8.1. Investigational Treatment/Strategy/Procedure

Upon the patient’s arrival in the operating room, a thoracic epidural is placed by the anesthesiologist. This involves inserting the catheter into the epidural space, but initially no local anesthetic is injected through the epidural catheter. The conduct of general anesthesia—its induction and maintenance—is left to the discretion of the attending anesthesiologist in the operating room. At induction, lidocaine is administered intravenously at 1.5 mg/kg as a bolus, followed by a continuous IV infusion at 2 mg/kg/h until surgical closure, in accordance with SFAR guidelines. The use of intravenous lidocaine in this manner is consistent with its approved labeling. At surgical closure, the lidocaine infusion is stopped, and the epidural is activated with ropivacaine 1 mg/mL, given as an initial bolus of at least 5 mL and then continued at a minimum rate of 5 mg/h for 24 hours postoperatively. The use of ropivacaine in this manner is also in line with its approved labeling. As part of this study, blood samples will be taken to measure plasma lidocaine levels at: 30 minutes after the induction bolus, at the end of the continuous infusion, and 2 hours after the start of the epidural ropivacaine infusion. Blood samples to measure plasma ropivacaine levels will also be taken: 2 hours after the start of the epidural, and 24 hours after the start of the epidural. Each blood sample is 6 mL.

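### The primary any-sample percentage cannot show slower lidocaine elimination as harm: it is blind if only the upper limit counts, and inverted if the 1.4 µg/mL floor counts too

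*Protocol*

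**What the plan says.** All references are to the Protocol.

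- **Primary rule, section 12.2:** "We will calculate the percentage of patients who have at least one plasma concentration of ropivacaine or lidocaine outside the safe range". It is reported with a 95% confidence interval.
- **Range, section 5.1:** "for lidocaine, the safe plasma range is 1.4 to 6 µg/mL". This has a floor and a ceiling. The same section also gives an upper-only rule: "Any single measurement above the toxicity threshold will be considered an occurrence of toxicity". Section 3.3 puts the ceiling elsewhere: "the therapeutic plasma range is 1.4 to 5 µg/mL, and toxicity can begin at concentrations above 5 µg/mL". The floor is 1.4 in both places.
- **Timing, section 1:** "The epidural ropivacaine infusion will be started at the same time the lidocaine infusion is stopped". Section 8.1 agrees: "At surgical closure, the lidocaine infusion is stopped, and the epidural is activated with ropivacaine 1 mg/mL".
- **Lidocaine samples, sections 3.3, 5.1 and 6.1:** 30 minutes after the bolus, at the end of the infusion, and 2 h after the epidural starts. The schedule table in section 10.2 instead labels the third visit as 2 h after surgery.
- **Purpose of the third sample, section 3.3:** among other things, to show whether lidocaine's "decline follows the expected pattern when another local anesthetic is present". The reference given there is "The half-life of IV lidocaine is 80–110 minutes".
- **Other analysis, section 12.2:** quantitative variables are summarised by mean, standard deviation, median and range. No analysis pairs the stop level with the 2 h level.

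**The concern.** The first two lidocaine samples precede any ropivacaine, so they cannot carry an effect of ropivacaine on lidocaine. Only the third can, and it is drawn when lidocaine has been washing out for about two hours. A rule that asks whether any sample lies outside limits then treats the third sample in one of two ways. If only high levels count, the sample is redundant once the stop sample is known. If low levels count too, the sample mostly records normal washout as an event.

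At stake is the reading of the primary result. Sections 1 and 3.4 plan to standardise practice on a demonstration that the combination is safe. A low percentage could be taken to include reassurance about lidocaine elimination, which the rule cannot give. On the two-sided reading, a low percentage could even be the product of impaired elimination.

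**Working it through.** **The plan's own precision figures.** With n = 50, the half-width 1.96 × √(p(1−p)/n) is 8.3% at p = 10% and 13.9% at p = 50%. These match the stated ±8% and ±14% after rounding. The concern does not affect them, but the assumed 10% matters in step 4.

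**Step 1: expected decline.** For a single-exponential decline, C(2 h)/C(stop) = 2^(−t/half-life), where t is the time since the infusion stopped.

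| t | half-life 80 min | half-life 110 min |
|---|---|---|
| 120 min (2 h after epidural start) | 0.35 | 0.47 |
| 150 min (2 h after surgery, if the infusion stops 30 min before the end) | 0.27 | 0.39 |

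At 120 min a doubled half-life gives 0.59 to 0.69, and no elimination gives 1.

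**Step 2: upper limit.** The ratio never exceeds 1. A stop level of 6 µg/mL becomes 2.12 to 2.82 at 2 h with the quoted half-life, 3.57 to 4.11 if the half-life doubles, and 6.00 if elimination halts. To exceed 6 at 2 h with the quoted half-life, the stop level must exceed 12.8 to 17.0, and that patient is already counted at stop. The same logic holds for a ceiling of 5 and for 150 min. The true 2 h level therefore adds no upper exceedance, however slow elimination becomes.

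**Step 3: lower limit.** The 2 h level is below 1.4 whenever the stop level is below 1.4/ratio:

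- quoted half-life: stop level below 2.98 (1.4/0.469) to 3.96 (1.4/0.354);
- doubled half-life: below 2.04 to 2.35;
- no elimination: below 1.40.

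The slower the elimination, the fewer patients count as outside the range.

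**Step 4: size under assumptions.** The Protocol gives no expected stop level or spread, so these are assumed. Take lognormal stop levels with geometric mean 3 µg/mL and CV 30%, and a lognormal half-life with mean 95 min and CV 25%, at 120 min:

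| Elimination | Patients below 1.4 at 2 h |
|---|---|
| normal | about 67% |
| half-life × 1.5 | about 33% |
| half-life × 2 | about 17% |
| none | about 0.5% |

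The range is wide. I varied the median stop level from 2 to 4 µg/mL with CV 30% or 50%, fixed the half-life at 80 or 110 min, and counted patients outside 1.4 to 6 at stop or at 2 h. This gives 24% to 99% with normal elimination and 1.4% to 23.5% with none. The 10% assumed in section 12.1 is hard to reconcile with the two-sided rule in any of the normal-elimination cases.

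**Step 5: assay error.** With a 10% assay CV on each sample and no elimination at all, a measured 2 h level above 6 after a measured stop level of 6 or less occurs in 0.6% of patients (geometric mean 3, CV 30%), 3.1% (4, CV 30%) and 3.4% (4, CV 40%). With the half-life × 1.5 or × 2 it is essentially zero.

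**The case against.** **The rule does react.** A reader might infer that the lidocaine result is the same whatever happens to elimination. That is true only under the upper-only sentence in section 5.1. Under the wording of section 12.2 the percentage moves a great deal, but downwards as elimination slows.

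**Interaction is not an objective.** The primary objective is to evaluate concentrations, and the hypothesis in section 3.2 concerns toxic thresholds. If elimination slows but no level crosses a threshold, an upper-only count reports that hypothesis correctly. This stands. The pattern of decline is a stated reason for one sample, not an endpoint, so the trial cannot be faulted for failing to test it formally.

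**The levels will be seen anyway.** A reader might infer that the 2 h values survive only as a yes/no count. They do not: the general summaries in section 12.2 would show them, and an analysis plan not shown here could add more. What those summaries do not give is the within-patient decline. The inversion also lies in the primary rule that the Protocol itself fixes.

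**New exceedances are possible.** A reader might infer that the 2 h sample can never add one. That holds for true levels. Assay error can add a few (step 5), and if the stop sample is missing the 2 h sample may be the only one to show an exceedance.

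**A formal flag would mislead.** It is tempting to declare slower decline when the 95% interval for the mean ratio lies above 0.47. Under the model of step 4 with 10% assay error and no interaction, that flag fires in about 9%, 66% and 98% of trials if the true mean half-life is 120, 130 or 140 min. The Protocol does not tie its 80 to 110 min to this surgical population, there is no control arm, and 0.47 applies only at 120 min. This objection stands and shapes the fix.

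**Conclusion.** The point holds in this form: the any-sample percentage cannot flag slower lidocaine elimination under the combination as harm. It is blind if only the upper limit counts and inverted if the literal two-sided range counts, whereas section 3.3 gives the 2 h lidocaine sample the task of showing the decline.

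The upper-limit result needs only that no lidocaine is given after the stop, that the stop sample is available, and that assay error is set aside. It does not depend on the half-life or on whether the ceiling is 5 or 6. A faster early distribution phase would strengthen it. The direction of the inversion follows from the 1.4 floor. Its size (about 67% falling to 0.5% in the worked case) rests on assumed stop levels.

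The documents do not support a claim that the plan is indifferent to elimination on every reading, or that it promises a formal interaction test. The ropivacaine part of the rule is unaffected.

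**What to change.** Change section 12.2, using samples already drawn:

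1. Apply only the upper limit in the safety percentage, so that a 2 h lidocaine level below 1.4 µg/mL is not a safety event. Reconcile the ceilings in sections 3.3 and 5.1 so that one limit is stated.
2. Add a descriptive analysis. For each patient, compute C(2 h)/C(stop) and the apparent half-life, ln 2 × elapsed time / ln(C(stop)/C(2 h)), from the actual stop and sampling times. Report geometric means with 95% confidence intervals beside the values implied by 80 to 110 min at the actual elapsed time (ratio 0.35 to 0.47 at 120 min, 0.27 to 0.39 at 150 min). Attach no pass/fail flag.
3. State that the any-sample percentage describes exceedance only and will not be used to conclude that the combination leaves lidocaine elimination unchanged.

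The third sample's timing in section 10.2 should be reconciled with sections 3.3, 5.1 and 6.1.

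The cost is one paragraph and the recording of actual times, with no added patients or blood. The limitation is that the reference is a quoted half-life rather than a control arm, so the ratio is supportive and can neither prove nor exclude an interaction.
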